### Screening examinations

Classical (secondary) preventive approaches for C&A in Germany are particularly the so called “U examinations” for the early detection of health disorders and abnormalities in development, introduced in the 1970s. Up to the age of 6, the U1 to U9 are carried out, which consequently contribute to the necessary treatment and support of the families. In addition, C&A between the ages of 12 and 14 are again entitled to a preventive examination (J1). Additional examinations, such as the U10, U11 and J2, have long been recommended by paediatricians, but have not yet been included in the benefits catalogue of the statutory health insurance (Gesetzliche Krankenversicherung, GKV) [3]. In addition to the established examination, these early screening measures also include questionnaire concepts and medical consultation concepts, as demanded by the Professional Association of Paediatricians and Adolescent Physicians (Berufsverband der Kinder- und Jugendärzte, BVKJ) for all early screening measures [4]. While the participation rate in the early screening measures in childhood (U1-U9) is more than 90% in each case, this proportion decreases steadily in adolescence [5, 6]. Only 46–48% of young people make use of J1. There are clear regional differences, with the federal states of Berlin, Brandenburg and Mecklenburg-Western Pomerania lying in the federal average with 37–55% [7]. This typical age dependency is also evident in the use of paediatricians: The older the C&A, the more frequently families switch from paediatricians to general practitioners. On the one hand, this can be attributed to the fact that starting from age 11 self-initiated physician attendance increases and thus the decision of whether to attend a physician is no longer reserved to the respective parents alone. However, a predominantly self-determined access to outpatient care can be assumed at the earliest from the age of 16 [5]. On the other hand, the interruption between the statutorily determined last U9 in childhood (between 60th and 64th month of life) and the later J1 in adolescence (between 12 and 14 years) means that the latter is much less accepted. In particular, children between the ages of 11 and 13 have the lowest demands on outpatient medical care [5].

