### Intervention

In 2007, AOK Nordost, a regional health insurance in the federal states of Berlin, Brandenburg and Mecklenburg-Western Pomerania, developed a programme for the early detection of diseases in C&A. The programme“AOK-Junior” is organised on the basis of a selective contract, which means that it is an individual contract concluded between AOK Nordost and a single service provider, in this case the Professional Association of Paediatricians and Adolescent Physicians (Berufsverband der Kinder- und Jugendärzte [BVKJ]). Selective contracts contain additional medical services with individual health insurance providers that transcend the legally defined medical care. This contributes to the assessment of innovative treatment approaches and can serve as a test for the possible inclusion of a medical service in the in the statutory health care system [15]. The existing selective contract is based on the special care regulations. They are intended to expand the scope for the health insurance to design their own plans and to remove bureaucratic barriers to selective contracts. Contracts for innovative and effictive services will be made possible which have not yet found their way into the standard health care system. The special care contracts are intended to network different performance sectors with each other and to enable interdisciplinary, multidisciplinary care.

By taking part, AOK-Junior offers families the opportunity to identify and treat their children with diseases at an early stage in order to avoid secondary diseases in the long term. On the other hand, competencies can also be strengthened in order to develop health awareness as a prerequisite for a healthy life [6]. This is especially true if children are included in the programme from the very beginning. Pediatricians thus act as gatekeepers and can contribute to the improvement of comprehensive and holistic care for C&A. The funding agencies also have the opportunity to specifically adapt to the needs and problems of their insured population by means of a tailor-made selective contract [15].

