The selective contract “Pediatric-centred integrated care AOK-Junior (AOK-Junior)” completes the legally defined medical care for insured persons up to the age of 18 in cooperation with qualified paediatricians. AOK-Junior focuses on health protection, early detection and prevention with the aim of maintaining C&A’ health and detecting and preventing diseases at an early stage. By participating in AOK-Junior, quality, service and coordination of treatment and prevention for C&A should be improved compared to standard care.

The AOK Nordost is responsible for preventive measures in addition to program development. The target group of this contract is therefore the entire population of children and young people insured with AOK Nordost (approx. 250,000) and their parents. The number of participating insured persons is approximately 65,000 C&A (August 2019). Thus, more than one fifth of the C&A insured under the AOK Northeast insurance participate in AOK-Junior.

Responsible for the implementation of the defined services is the BVKJ-Service GmbH. BVKJ-Service GmbH represents the interests of approx. 560 paediatricians (August 2019) participating in AOK-Junior.

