### Medical services of the selective contract

At the centre of the health care provision for C&A within the framework of AOK-Junior is the paediatrician, who coordinates the general medical-paediatric and specialist care. AOK-Junior comprises the following modules:
The performance module includes additional early detection examinations: The focus of the **U10** (age 7–8) is, among other things, the recognition of motor development disorders as well as developmental and behavioural disorders. The **U11** (age 9–10) includes, among other things, the recognition of school performance disorders, socialisation disorders, behaviour harmful to health as well as tooth, mouth and jaw anomalies. The focus of **J2** (age 16–17) is the recognition/treatment of puberty and sexuality disorders, posture disorders, goitre formation as well as diabetes prevention and counselling in questions of behaviour, socialisation, family and sexuality.Performance module **Allergic Rhinitis**: The module promotes specific immunotherapy (SIT) for AOK-Junior participants with allergic rhinitis. By using a reminder system, the high current dropout rate is intended to be reduced and the rate of successfully completed hyposensitizations increased.Performance module **Ophthalmologic Early Screening Examination**. The module is intended to promote the early detection of eye diseases, visual defects and strabismus in children between the ages of 32 and 42 months. An individual consultation should avoid eye damaging influences and behaviours.**Lung Check** performance module. The aim of the Lung Check module is to prevent a chronic respiratory disease, to provide information about possible therapies and to positively influence the course of the disease. The preventive care benefit can be claimed by 6- to 7-year-olds under certain conditions and includes an outpatient pneumological examination as well as a health education consultation.**Skin Check** performance module. The skin check includes additional measures for the early detection and treatment of chronic skin diseases. Individual consultations are intended to help avoid skin-damaging influences and behaviours. The first skin check is aimed at 2 to 5-year-olds, the second at 13 to 17-year-olds.Performance module **Dental Health**. AOK-Junior participants receive a subsidy if the premolars have to be sealed. In addition, professional dental cleaning for AOK-Junior participants with ongoing orthodontic treatment can be subsidized.Performance module **Target Agreement on Overweight**. In order to reduce the morbidity and mortality risk of overweight or obese AOK-Junior participants in adulthood, a target agreement for weight reduction is concluded with either the participants or one parent. It is also essential to provide information on overweight and obesity, their serious health consequences and weight reduction options. If the goals are achieved, there is a bonus gift for the AOK-Junior participants. The measure is intended to bring about a change in dietary and movement habits.

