### Study population

The underlying study population consists primarily of an IG and a CG at paediatricians as well as C&A level. The AOK-Junior selective contract is implemented in entire catchment area of the AOK Nordost. At the level of paediatricians, all participating physicians are included in the quantitative survey. The CG includes doctors who are also organised in the BVKJ but do not participate in the selective contract AOK-Junior. For the inclusion of the CG, it is considered that these are active in catchment areas that are as comparable as possible. A sub-sample will be taken for the qualitative surveys. Thereby, an adequate representation of the range of catchment areas of established paediatricians is taken into consideration.

At the level of the insured, the study population is drawn on the basis of routine data. The participants of the IG are C&A from birth up to and including the age of 17. Thus for each module its own population is needed. The exception is the target agreement on overweight. In the CG are C&A who are also insured with the AOK, but who do not participate in the AOK-Junior prevention programme. In order to ensure comparability between participating and non-participating insured persons, a CG is formed for the IG on the basis of routine data using the characteristics of sex, age and comparable region by means of PS matching.

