#### Quantitative analyses

The data evaluations are initially performed descriptively. The hypotheses developed are also tested for inferential statistics. In order to ensure comparability between participating and non-participating insured persons, a CG is formed for the IG on the basis of the routine data using the characteristics gender, age and comparable region. Participants from both groups are brought together with PS matching at the individual level. The analyses of the primary data take into account in particular covariates for which it was not possible to match at the secondary data level, such as socio-economic status and migration background. The influence of the selective contract is checked using ANCOVA. The analyses are carried out with the software programs SAS, SPSS and Microsoft Excel.

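### Child controls are matched on sex, age and region only, so the detection contrast mixes the contract's added services with being in paediatric care, chiefly in adolescents

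*Protocol article*

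**What the plan says.** The Study population section defines child controls as follows: "In the CG are C&A who are also insured with the AOK, but who do not participate in the AOK-Junior prevention programme". Comparability is to come from "using the characteristics of sex, age and comparable region by means of PS matching". The Quantitative analyses section repeats the same set: the control group is formed "on the basis of the routine data using the characteristics gender, age and comparable region". The sample size section gives the ratio as 1:1 and defines the routine-data intervention group as the patients who used the services.

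The contract is built around one type of physician. According to the Intervention section it "completes the legally defined medical care for insured persons up to the age of 18 in cooperation with qualified paediatricians", and "Pediatricians thus act as gatekeepers". Under Medical services of the selective contract, the centre of care "is the paediatrician, who coordinates the general medical-paediatric and specialist care".

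The Screening examinations section of the Background describes how provider use changes with age: "The older the C&A, the more frequently families switch from paediatricians to general practitioners". It adds that "children between the ages of 11 and 13 have the lowest demands on outpatient medical care".

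The Objectives section attributes the difference between the groups to participation in the contract, compared with standard care. H1 (earlier detection) and H2 (more detection) are assessed in the routine-data cohort.

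**The concern.** Children in the intervention group have used a paediatrician-coordinated programme. A control child needs only to be insured and not enrolled, and may see a paediatrician, a general practitioner or no physician. Matching on age does not remove this difference. At the same age, one group is in paediatric care and an unknown part of the other is not.

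A diagnosis enters billing data only after a contact. Control children with fewer contacts, or with a different type of physician, could therefore show later and fewer diagnoses even if the contract's extra examinations added nothing. That would affect H1 and H2, and also H5, because cost per detected case has the number of detected cases in its denominator. The project aims to judge the contract and its service modules, and a contrast that also contains the effect of having a paediatrician cannot separate the two.

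**Working it through.** **1. What is controlled in the routine-data comparison**

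| Item | Intervention group | Control group |
|---|---|---|
| Entry rule | used the contract's services | AOK-insured, not participating |
| Link to a paediatrician | care coordinated by one | none required |
| Matched on | sex, age, region | sex, age, region |
| Provider type or prior use | not matched | not matched |

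The further covariates named under Quantitative analyses (socio-economic status, migration background) are for the primary survey data. They do not enter the routine-data cohort. At physician level the article does restrict controls, to doctors in the same paediatric association working in comparable areas. It sets no parallel condition for children.

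**2. Where the problem should be largest**

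The article places the lowest outpatient use at 11–13 years and describes a gradual move to general practitioners with age. Among the modules with a stated age range, the second skin check (13–17) and J2 (16–17) are the only ones for adolescents. U10 (7–8), U11 (9–10), the eye screening (32–42 months), the lung check (6–7) and the first skin check (2–5) all lie at age 10 or below.

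**3. Size under a null contract effect**

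The article gives no figure for this point, so there is none to reproduce. Its survey sample size (1096 net, 1096/0.40 = 2740 invited) concerns quality of life and has no bearing here.

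Both inputs are assumptions:
- q = share of matched controls outside paediatric care
- r = detection rate outside paediatric care relative to inside it

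Let d be the detection rate in paediatric care, and let the contract have no effect. The intervention rate is d and the control rate is (1 − q)d + q·r·d, so

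ratio = 1 / (1 − q(1 − r)).

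Example: q = 0.25, r = 0.5 gives 1/(1 − 0.125) = 1.14.

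| q | r = 0.5 | r = 0.7 | r = 0.9 |
|---|---|---|---|
| 0.10 | 1.05 | 1.03 | 1.01 |
| 0.25 | 1.14 | 1.08 | 1.03 |
| 0.40 | 1.25 | 1.14 | 1.04 |
| 0.60 | 1.43 | 1.22 | 1.06 |

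The ratio is 1 only if q = 0 or r = 1.

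**4. Would it be mistaken for a finding?**

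Assume 20,000 children per group and 5% detection in the intervention group. The control rate at a spurious ratio of 1.14 is 5%/1.14 = 4.39%. The standard error of the difference is √(0.05·0.95/20,000 + 0.0439·0.9561/20,000) ≈ 0.0021, so z ≈ 0.0061/0.0021 ≈ 2.9. The chance of two-sided p < 0.05 is then about 83%. With 1,000 per group it is about 10%.

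**The case against.** The strongest reply is that the stated comparator is standard care, and standard care for adolescents includes general practitioners and non-use. Coordination by a paediatrician is itself part of the contract, so keeping children in paediatric care may be part of its effect. On that view, restricting the controls answers a different and narrower question. This stands: the contrast is interpretable as programme versus standard care. What it cannot do is isolate what the added examinations and modules contribute.

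A reader might infer that the programme can be entered only through a paediatrician, so that control children without one could not have joined. The article does not say this. Gatekeeping and coordination describe a role in care, and no enrolment rule is stated. The target group is the whole insured child population, and some modules involve a pneumological examination or dental subsidies. Nor are the controls wholly outside paediatric care; they are a mixture in unknown proportions.

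A reader might also infer that the bias demonstrably grows with age, or that it already bites at U11. The article gives no share at any age and nothing on relative detection. U11 is at 9–10 years, below the band of lowest use.

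Finally, the article announces a detailed study plan, and claims-based eligibility windows are often left to such a plan. That does not dispose of the point, because the article fixes a specific control definition and a specific matching set, twice, and neither contains any measure of access to care.

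**Conclusion.** The point holds as a confounding problem in the routine-data comparison for H1 and H2. The stated control rule and matching set leave access to paediatric care uncontrolled, and the article's own background says that this access changes with age. The adolescent modules are the most exposed.

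The size is not known. The range of about 1.01 to 1.43 rests entirely on the assumed shares (10–60%) and relative detection (0.5–0.9), on a contract effect of zero, and on all intervention children being in paediatric care. If some of them were not, the ratio would lie closer to 1. At the low end the effect is negligible. At the high end it could pass for a programme effect in a large cohort. The documents do not support calling the whole contrast invalid. They support saying that it answers the broad question and not what the contract's services add for children in paediatric care.

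**What to change.** In the Study population and Quantitative analyses sections, for the routine-data comparison:

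- Add paediatrician contact and outpatient use in the four quarters before a common index date to the propensity score. Alternatively, restrict both groups to children with a paediatrician contact in that window.
- Set the index date per module, give each control the index date of its matched participant, and use the same look-back in both groups. Tying the window to enrolment for participants and to some other date for controls could test the two groups at different ages.
- For infants, who have no look-back, do not condition on contact in the index quarter, because that contact may be the detection visit.
- Keep the unrestricted comparison as the standard-care contrast and report the two side by side, by age band.

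The cost is modest: extra variables from routine billing data already planned for use, assuming that these identify physician specialty, which the article does not list. The control pool is about 250,000 − 65,000 = 185,000 before any restriction and would shrink under one. The restricted result would apply to children already in paediatric care. For participants enrolled well before the index date, look-back contact may partly reflect the programme itself, which is another reason to keep both analyses.

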#### Evaluation of the structural quality

The evaluation of the structural quality is carried out on the basis of cross-sectional analyses of the available routine data. Reference data are used to evaluate the degree of achievement. In addition, primary data on structural features are collected as part of the quantitative cross-sectional survey of paediatricians. In this context, the cross-sectional design is well suited to examining the absolute and relative frequency of structural features between participating and non-participating physicians or insured persons. The structural characteristics of the physicians include, for example, region, group of specialists, size of practice, practice kind (single practice, joint practice or practice communities), number of patients treated per quarter, age and sex. Among the structural characteristics of insured persons are e.g. age, sex, nationality, income, education and occupational status (of parents) and chronic diseases (diabetes mellitus, ADHD, asthma, allergy and obesity).

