#### Evaluation of outcomet quality

The outcome quality is assessed from the routine data as a longitudinal study in the design of a cohort study. Cohort studies are well suited to examine the frequency and timing of a disease. As the AOK-Junior programme has been implemented since 2007 and routine data are available, data can be analysed over a longer period of time than is usual for prospective studies. In addition, practicable aspects speak in favour of the method: Overall costs are lower and the data are available more quickly. The outcome quality is assessed on the basis of the time of detection (see hypothesis 1) and the incidence rate (see hypothesis 2) of a chronic disease. The secondary preventive measure AOK-Junior aims at the early detection of disease. The control group is generated by propensity score matching (PS matching).

Further relevant result parameters are collected by means of quantitative cross-sectional surveys. For example, the health-related quality of life of C&A, which is assessed via KIDSCREEN-27 [16, 17]. As a result of the increase in chronic degenerative diseases, the health-related quality of life is becoming increasingly important as a outcome parameter [1, 2].

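### The routine-data control group is matched on sex, age and region only, so prior morbidity and health-care use are not controlled in any step described for H1, H2 and the cost analyses

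*Protocol article*

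**What the plan says.** All references are to the protocol article.

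- **Matching variables.** The section on the study population says that "a CG is formed for the IG on the basis of routine data using the characteristics of sex, age and comparable region", using propensity score matching. The section on quantitative analyses repeats the list: "on the basis of the routine data using the characteristics gender, age and comparable region". Neither place marks the three characteristics as examples.
- **Purpose.** The matching is done "In order to ensure comparability between participating and non-participating insured persons".
- **What rests on it.** The section on outcome quality assesses the programme by "the time of detection (see hypothesis 1) and the incidence rate (see hypothesis 2) of a chronic disease", read from the routine-data cohort with this matched control group. The health economic section builds cost per detected case and avoided follow-up costs on those results.
- **Further covariates.** The section on quantitative analyses says: "The analyses of the primary data take into account in particular covariates for which it was not possible to match at the secondary data level". The examples given are socio-economic status and migration background. ANCOVA is named in the next sentence.
- **Who is in the IG.** The sample size section puts into the routine-data IG all patients who took up the services and draws the CG from the same data at 1:1.

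**The concern.** A propensity score removes confounding only by the variables it contains. Here those are three demographic characteristics, while the decision to take part depends on much more. The process evaluation intends to ask families why they did or did not join, so the protocol itself treats enrolment as a choice. The IG is narrowed further to users of the services, whereas the CG is defined by not participating.

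The background section shows how much children of the same age can differ in their use of care. Families increasingly move from paediatricians to general practitioners as children grow older, and only 46–48% of adolescents attend J1. A child who already sees a paediatrician regularly, or who has a chronic condition, may be more likely both to enrol and to receive a further diagnosis or incur costs, with or without the programme.

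At stake is the main question. If the IG shows earlier or more frequent detection, the matched comparison as described could not separate a programme effect from who joins. Cost per detected case and avoided follow-up costs would inherit the same problem.

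**Working it through.** The protocol gives no figure for this bias, so there is none to reproduce. The check has three steps.

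**1. Is enrolment selective enough to matter?** The intervention section gives about 65,000 participants among about 250,000 insured children: 65,000 / 250,000 = 26%, which agrees with its statement of more than one fifth. The remaining pool is 250,000 − 65,000 = 185,000. Participants are a minority who chose to join.

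**2. How large could the bias be?** For one omitted binary confounder with prevalence p1 in the IG and p0 in the CG, and risk ratio RR for the outcome, the spurious ratio with no true effect is

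B = (1 + p1(RR − 1)) / (1 + p0(RR − 1)).

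All inputs below are assumptions; the document supplies none.

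| p1 | p0 | RR | B |
|---|---|---|---|
| 0.55 | 0.45 | 1.5 | 1.275 / 1.225 = 1.04 |
| 0.60 | 0.40 | 1.5 | 1.30 / 1.20 = 1.08 |
| 0.60 | 0.40 | 2 | 1.60 / 1.40 = 1.14 |
| 0.70 | 0.40 | 3 | 2.40 / 1.80 = 1.33 |

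**3. Would such a bias be declared significant?** With n per group and incidence q (assumed 5%), the standard error of the log ratio is about sqrt(2(1 − q) / (q·n)). For B = 1.083, ln B = 0.080.

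- n = 65,000: SE = sqrt(1.9 / 3,250) = 0.024, z ≈ 3.3.
- n = 5,000: SE = sqrt(1.9 / 250) = 0.087, z ≈ 0.9.

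For B = 1.14, the chance that bias alone gives two-sided p < 0.05 is:

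- 65,000 pairs, 5% incidence: about 100%
- 20,000 pairs, 5% incidence: about 88%
- 5,000 pairs, 5% incidence: about 34%
- 5,000 pairs, 2% incidence: about 16%

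The figure of 65,000 is total enrolment and so a ceiling. The IG comprises service users, the study population section calls for a separate population for each module (overweight excepted), and the long-term cost analysis is confined to Brandenburg. Significance therefore depends on the module. The bias in the estimate does not shrink with sample size.

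**The case against.** The case for the plan has several parts.

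- **A journal article condenses.** Outcome-model covariates for the routine data may be set in a fuller plan, and the ANCOVA sentence is not expressly confined to the survey. This stands in part: absence of outcome-model adjustment is inferred. The matching list, however, is stated positively twice, and the extra covariates are described for the primary data.
- **The limit on socio-economic status and migration is disclosed.** The article speaks of "covariates for which it was not possible to match at the secondary data level, such as socio-economic status and migration background". A reader might infer that H1 to H5 are wholly without control for these; the text is not that firm. Nor does the disclosure name prior morbidity or use.
- **Data fields are not listed.** A reader might take it as established that the insurer's data hold every variable needed, citing "chronic diseases (diabetes mellitus, ADHD, asthma, allergy and obesity" among the characteristics of the insured. That list also contains income and education, so it is not an inventory of routine-data fields. Availability is an inference: time of detection and incidence are read from the routine data, so diagnoses must be there, and the measurements section brings in performance and accounting data.
- **Age balance.** A reader might add that a score balances age only on average while modules have narrow age windows. With module-specific populations, the windows themselves limit the age gap, so this is not supported.
- **Statistical significance.** A reader might infer that any modest bias would be significant in so large a cohort. At module size this need not be so.
- **Children enrolled from birth** have little or no earlier history to match on. This stands and limits the remedy.

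**Conclusion.** The concern holds in this form: the matching characteristics as stated are too few to support the claim that comparability is ensured, and prior morbidity and health-care use are left out of every control step described for the routine-data outcomes. The point carries most weight for modules at older ages, where a history before enrolment exists.

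The document does not show that the results will be biased, by how much, or in which direction. The range of about 1.04 to 1.33 rests on assumed prevalences and risk ratios for a single binary confounder and serves only for scale. The conclusion also rests on two readings of the text: that the additional covariates belong to the survey analyses, and that the insurer's data contain earlier diagnoses, contacts and costs. Because the remedy is a specific and cheap change to a stated method, it should be made before the routine data are analysed.

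**What to change.** For each module:

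1. Set an index date for IG and CG children, so that history is counted up to a comparable point in both groups.
2. Where the outcome is new detection, exclude children who already have the target diagnosis at that date. They are no longer at risk, so exclusion is needed rather than matching on that diagnosis.
3. Keep sex, age and region, and add to the score the pre-index variables available in the insurer's performance and accounting data: other chronic diagnoses, attendance at U and J examinations, paediatrician and specialist contacts, hospital stays, prescriptions and total costs. Confirm first that these fields can be supplied.
4. Report balance by standardised differences, for example below 0.1, and adjust the outcome model for the same variables.
5. For children enrolled at or near birth, state that the result is open to residual confounding, and do not claim that comparability is ensured.

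The cost is more programming and a wider extraction from data already in use. Some IG children may remain unmatched. The overall pool of about 185,000 non-participants helps, but the document gives no module-level or Brandenburg counts, so the number lost cannot be stated in advance and should be reported.
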